### Setting

The participants’ personal setting can be any environment of their choice that has internet access. In 2011, 94% of the Dutch population had internet access in their homes, and approximately 87% used the internet (almost) every day [41]. In this way, patients throughout the country can participate in the study. The therapists’ setting will be the department 'Web-based interventions’ of Tactus Addiction Treatment, which is located in Enschede, the Netherlands.

### Participants

The study population will consist of female patients with BN, BED and EDNOS. Based on the results of our pilot study, we will exclude males and patients with AN, as these patient groups were a minority in our pilot study. Male patients and patients with AN will be offered the possibility of participating in the regular web-based treatment program without participating in the RCT.

### Inclusion criteria

The inclusion criteria for the present study are: 1) female; 2) aged 18 years or older; 3) a diagnosis of BN, BED or EDNOS; 4) access to and ability to use the internet; 5) the ability to read and write Dutch; and 6) have given informed consent.

### Exclusion criteria

The exclusion criteria for the study are: 1) body weight less than 85% of ideal body weight; 2) other psychological and/or pharmaceutical treatment for eating disorders in the past six months; 3) critical suicidal ideation (suicidal plans or attempted suicide in the past month, or attempted suicide once and suicidal thoughts in the past month); 4) being pregnant; and 5) planning to be absent for at least four weeks during the intervention period.

### Recruitment

For recruitment, self-selection through a placed advertisement will be used. Information regarding the web-based treatment program and the trial can be found on the Dutch website http://www.etendebaas.nl and on other Dutch eating disorder-related websites and forums. We will also place targeted advertisements in Dutch newspapers and attempt to obtain free publicity for the intervention and the study in newspapers and magazines.

### Procedure

Participants will receive an email with an attachment containing a description (in Dutch) of the research project and the web-based intervention. Written informed consent must be provided by each participant prior to randomization. The consent form will include information regarding withdrawal of consent, providing personal information, and GP data.

Each participant will also complete the baseline questionnaire (Q0), which is an extensive online questionnaire consisting of questions regarding eating attitudes and behaviors, body dissatisfaction, physical and mental health, and the personal situation of the participant. Based on the replies given in the baseline questionnaire, the investigator will evaluate whether the participant meets the inclusion or exclusion criteria of the study. An eating disorder diagnosis will be determined using an online self-report questionnaire based on the DSM-IV criteria for BN and the criteria described in Appendix B of the DSM-IV-TR for BED. The Dutch version of the Mini-International Neuropsychiatric Interview–Plus (MINI-Plus) [42,43] will be used as a guideline. The MINI-Plus is an appropriate measurement for daily psychiatric practice and research purposes to determine DSM-IV diagnoses in a standardized way [44]. Participants with one or more eating disorder characteristics who do not meet the criteria of BN or BED will be diagnosed with EDNOS. An exception will be made for those participants who meet the exclusion criterion “body weight less than 85% of ideal weight” which will be measured using the weight table in the MINI-Plus part N (Anorexia Nervosa) [43,44]. To assess this exclusion criterion, the participants will be asked for their height and lowest body weight in the three months prior to the study.

Participants who do not meet the inclusion criteria and are therefore not eligible to participate in this study will be informed of the possibility of participating in the standard web-based treatment program without having to participate in this study. Participants who cannot participate in the web-based treatment program (for example, because they already receive treatment for their eating disorder at another institution or due to urgent medical reasons) will be referred to their GP or to a mental health institution.

### Study intervention

#### Experimental treatment group

The web-based treatment program is part of an online application for patients with eating disorders. The application also includes an informational website (http://www.etendebaas.nl) and a forum for peer support [38,40]. The contents and elements of the treatment program are based on two evidence-based techniques: Cognitive Behavioral Therapy [45-47] and Motivational Interviewing [48,49].

During the web-based treatment program, all participants will have their own therapist with whom they will communicate personally and asynchronously twice a week, solely through the internet. There will be no face-to-face or telephone contact during the treatment period, unless participants specifically request this. The asynchronous communication resembles email contact, but will take place within a secure web-based application. Participants will receive a response from their therapist within three working days. Asynchronous contact was chosen because it will give participants more autonomy to decide when to participate in the treatment program, and it enables them to think carefully about the responses they will give to the therapist. The intensive and personalized interaction between participants and their therapists is one of the most essential elements of the web-based treatment program and makes this intervention stand out from online self-help programs and minimal-contact therapies. The aim of the intense interaction is to optimize the relationship between the participants and their therapists, as the therapeutic alliance is positively associated with treatment outcome in face-to-face treatment [50,51] as well as web-based treatment [52,53]. However, so far the therapeutic relationship has not been studied extensively for web-based treatments on eating disorders [31].

All of the therapists working on the web-based treatment program will have a bachelor’s degree in nursing or social work or a master’s degree in psychology. Furthermore, they will complete an intensive two-day training program that focuses on motivational writing skills, treatment methods for patients with eating disorders, implementation of the treatment protocol, and the technical aspects of delivering this web-based intervention. Subsequently, all therapists will complete a full treatment program with a test patient, after which they can start under supervision as online therapists. Intensive supervision by highly experienced coaches will continue for at least three months, during which a coach will provide feedback on all therapists’ messages before they are sent to the participants. These participants may join the treatment program within their own personal environment at any time that suits them. Therefore, no pre-determined appointments will be required. The average duration of the web-based treatment program will be 15 weeks, with two contacts a week. Part 1 of the program will consist of four assignments and at least seven contacts between the participant and the therapist, with a focus on analyzing the eating attitudes and behaviors of the participant. At the end of Part 1, the participant will receive personal advice from the therapist. Part 2 involves six assignments and at least 14 contacts. This part of the treatment program will start with setting goals for eating behavior, exercising, weighing, and compensatory behaviors (if applicable). The participants will learn to reach these goals in five steps. In addition to receiving assignments, the participants will also receive psycho education and exercises. After completing the program, participants may take part in an aftercare program consisting of six weekly sessions. The purpose of this program will be to support participants in their efforts to maintain the changes achieved through the treatment program. During the sessions, the therapist will respond to participants’ messages and the information registered in the eating diary. Besides the aftercare sessions, there will be three follow-up contacts, 3, 6 and 12 months after completion of the treatment, in which the therapist will ask the participant to complete the follow-up questionnaire. The treatment sessions are presented in Figure 2.

**Figure 2 F2:**
[figure not shown]
Treatment sessions of the web-based treatment program.

All Dutch citizens have mandatory health care coverage. Dutch health insurance companies will reimburse costs participants incur by taking part in this web-based treatment program, with the possible exemption of a participant contribution up to 350 euro.

#### Waiting list control group (no-reply e-mail messages)

The participants in the waiting list control group will have to wait for 15 weeks after the randomization before they can start taking part in the web-based intervention. During this period, the participants will receive a no-reply email from the researcher every two weeks to keep them involved in the study. To avoid therapeutic support, the participants in the waiting list control group cannot reply to these messages. The email messages will include information about eating behaviors and body image, psycho education, motivational messages, and references to the informational website and online forum.

### Primary outcome measure

Primary outcome measure for this study will be an improvement in the eating disorder psychopathology. This will be measured with the Eating Disorder Examination Questionnaire (EDE-Q) [54,55]. The EDE-Q is a 36-item self-report questionnaire, derived from the Eating Disorder Examination Interview (EDE) [56]. The EDE-Q is widely used to assess the key behavioral features of eating disorders and the severity of the psychopathology of eating disorders. The EDE-Q consists of four subscales: Restraint, Eating Concern, Shape Concern, and Weight Concern. The items will be scored on a seven-point Likert-type scale ranging from 0 to 6. The scores on the four subscales account for the EDE-Q total score, which will be the primary outcome measure in this study. Validation studies of the EDE-Q have shown a high level of agreement between the EDE-Q and EDE in assessing the core attitudinal features of eating disorder psychopathology in the general population [54,57], among female substance abusers [58], and in clinical samples of both BN and BED patients [59,60]. Luce & Crowther [61] and Reas, Grilo & Masheb [62] also demonstrated acceptable internal consistency and test-retest reliability.

### Secondary outcome measures

#### Body dissatisfaction

The Body Attitude Test (BAT) developed by Probst and colleagues [63-66] is a 20-item questionnaire measuring the subjective perception and attitude of the participant against her own body. The items will be scored on a six-point Likert-type scale ranging from 0 to 5. A higher score represents a more disordered body experience. The cut-off score between patients with body dissatisfaction and patients without body dissatisfaction is 36 [65].

#### Physical health

The physical complaints related to eating disorders will be assessed using the Maudsley Addiction Profile-Health Symptom Scale (MAP-HSS) [67]. This is a 10-item structured interview, which was adapted from the health scale of the Opiate Treatment Index [68]. Each item will be scored on a five-point Likert-type scale ranging from 0 (complaint never present in the previous 30 days) to 4 (complaint always present in the previous 30 days), resulting in a total scale-score ranging from 0 to 40. In previous research among opiate users, the scores on the MAP-HSS were approximately evenly distributed, the internal consistency of the scale was satisfactory (α = 0.79), and the test-retest reliability of the scale was high, with an intra-class correlation coefficient amounting to 0.86 [67]. Because the MAP-HSS only measures general physical complaints, 15 additional items (dizziness/fainting; insomnia; hoarseness; sore throat; palpitations; diarrhea; constipation; hair loss/brittle hair; downy hair on face, arms, chest or back; fluid accumulation in the legs; dry/scaly skin; rapidly cold; dental problems; damaged back of the hand; swollen glands) will be added to measure eating disorder-specific physical complaints. The total score of physical complaints will be determined by dividing the sum of the scores on the MAP-HSS and the additional items by the total number of items (n = 25).

#### Body weight

Body weight will be measured with one item: 'What is your current weight?’ Participants will be asked to fill in their body weight in kilograms.

#### Mental health

The Depression Anxiety and Stress Scale-21 (DASS-21) [69] is a 21-item self-report questionnaire assessing levels of depression, anxiety and stress. Participants will be asked to respond to each item to indicate the extent to which it applies to them in the previous week. Each item will be scored on a four-point scale ranging from 0 (did not apply to me at all) to 3 (applied to me very much, or most of the time). The DASS-21 has been shown to have high concurrent validity (r = 0.84) and reliability (i.e. Cronbach’s alpha of 0.94, 0.87 and 0.91 for the subscales depression, anxiety and stress, respectively) [70].

#### Self-esteem

The Rosenberg Self-Esteem Scale (RSES) [71] is a widely used self-report questionnaire consisting of 10-items to measure an individual’s overall self-esteem. Higher numbers represent higher levels of self-esteem. The RSES consists of 10 statements, of which five are negative and five positive. It has been demonstrated to be highly reliable with Cronbach’s alphas in the range of 0.77 to 0.88 [72].

#### Quality of life

The EuroQol-5D (EQ-5D) [73] is a standardized measure of health status, which can be used in the clinical and economic evaluation of health care. The EQ-5D consists of the ED-5D descriptive system and the EQ-5D visual analogue scale (EQ VAS). The EQ-5D descriptive system will measure quality of life on 5 dimensions: Mobility, Self-care, Usual activities, Pain/discomfort, and Anxiety/Depression. There are three levels of severity for each item: (1) no problems, (2) some problems, (3) severe problems. The scores on the 5 dimensions will be combined in a 5-digit number describing the participant’s global health state. A total of 243 possible health states are described. The EQ VAS will record the participant’s self-rated health on a visual analogue scale ranging from 0 ('Worst imaginable health state’) to 100 ('Best imaginable health state’).

#### Social contacts

Social contacts will be measured using three dimensions of the MATE (Measurements in the Addictions for Triage and Evaluation) part 7 'Activities & Participation, Care & Support’: (1) interpersonal interactions and relationships, (2) important areas of life, and (3) social life [74,75]. The MATE was constructed according to the ICD and International Classification of Functioning (ICF) in the World Health Organization (WHO) classification system. The dimension 'interpersonal interactions and relationships’ consists of 5 items, which will be scored on a five-point Likert-type scale, ranging from 1 (no / not applicable) to 5 (completely). The dimensions 'important areas of life’ and 'social life’ both consist of 2 items, using the same five-point severity scale.

#### Motivation for treatment

To measure motivation for treatment, the TCU Motivation for Treatment (MfT) [76] will be used. The MfT questionnaire was originally developed to measure treatment motivation in people with alcohol dependence, therefore, some textual adjustments will be made to make it suitable for patients with eating disorders.

#### Therapeutic alliance

The Helping Alliance Questionnaire (HAQ) is an 11-item self-report questionnaire to give a quick and global impression of the perception of the quality of the working alliance between the participant and the therapist [77,78]. The questionnaire contains two scales: (1) 'cooperation’, reflecting the participant’s perception of the measure of help received from the care provider; and (2) 'helpfulness’, referring to the participant’s confidence in his or her own capacity to improve the situation.

#### Participants’ acceptability of the web-based treatment program and satisfaction with their personal therapist

At post-treatment, the participants’ acceptability of the program and satisfaction with their own personal therapist will be measured. The participants will be asked to identify those aspects of the treatment which they consider to be most important, and to indicate how pleasant, personal, and safe they found the treatment program. The participants will also be asked to confirm whether the web-based treatment program was effective for them and whether they would recommend the intervention to others. The participants will also have to rate the treatment program and their own personal therapist on a scale from 0 (very low) to 10 (very high). Finally, they will have the opportunity to provide additional comments.

### Sample size and power calculation

The sample size is calculated with the statistical power analyses program “G-power 3.1” by using a significance level of 95% (p < .05), a power of 80%, the same number of participants per condition (M 1:1), 2 groups, 2 measurements, a correlation among repeated measures of 0.95, a mean difference (MD) score of 1.0, and a standard deviation (SD within group) of 1.2. The MD and SD are based on the results of the EDE-Q total score during our first study among 28 participants (results have not been published). Based on this calculation 25 participants per condition (experimental treatment group, waiting list control group) will be needed. However, some participants will end the treatment program prematurely. In the first study this amounted to 46% of the participants. We expect this will be less during the RCT, given the inclusion and exclusion criteria, the written informed consent, and the completers rate within the RCT of Ruwaard & Lange [37]. We expect that at least 60% of the RCT participants will complete all treatment sessions of the web-based treatment program. This means that 42 participants per condition are needed. As we want to measure the effectiveness of the web-based treatment program for the specific eating disorder subtypes BN, BED and EDNOS, we will need 42 participants per condition for all of the individual subtypes. This brings the total number to 252 participants.

### Randomization

The participants will be randomized to either the experimental treatment group or the waiting list control group via computer-generated randomly varying block sizes (2, 4 or 8), stratified by type of eating disorder (BN, BED, EDNOS). Block randomization will ensure that equal numbers of participants will be recruited into each subgroup (respectively, 42 participants in the BN experimental group, BN control group, BED experimental group, BED control group, EDNOS experimental group, and EDNOS control group). The computer-generated randomization will be prepared by a research assistant who is not involved in either testing or implementing the intervention. The lead investigator will be responsible for the allocation of the participants to one of the two groups. She will contact the research assistant every time a new participant can be allocated to one of the two groups, in order to ask the research assistant to which group the next participant should be assigned. The lead investigator will then assign the participant to that group via the web-based application. The participant will receive an automatic email which will indicate the group to which she has been assigned.

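### Stratified blocks balance the arms within BN, BED and EDNOS but cannot secure 84 patients per subtype, and the article states no rule that does

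*Protocol article*

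**What the plan says.** Three parts of the protocol article bear on this point.

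- **Sample size and power calculation.** One comparison needs 25 per condition, raised to 42 for an expected 60% completion. Because effectiveness is to be measured within each subtype, "we will need 42 participants per condition for all of the individual subtypes", and the total becomes 252.
- **Randomization.** Allocation uses randomly varying blocks of 2, 4 or 8, stratified by BN, BED and EDNOS. The section then says: "Block randomization will ensure that equal numbers of participants will be recruited into each subgroup". It lists all six cells at 42 each.
- **Recruitment and Procedure.** Patients come forward on their own: "self-selection through a placed advertisement will be used". Subtype is established only from the baseline questionnaire, and EDNOS takes those who meet the criteria for neither BN nor BED.

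The article states no quota, cap or closing of enrolment by subtype.

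**The concern.** The sentence in Randomization credits a method with a property that it does not have. A block fixes how many of the next few patients in a stratum go to each arm. It does not decide which patients arrive. Stratified blocks therefore hold the arm numbers close together within BN, within BED and within EDNOS, and leave the three subtype totals to recruitment.

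The numbers matter because the trial is sized on them. One comparison needs 84 patients; the other 168 of the 252 are there so that each subtype can be assessed separately. If the only mechanism named for reaching 84 per subtype cannot deliver it, the stated basis for two thirds of the sample is not secured.

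**Working it through.** **Inputs, all from Sample size and power calculation.**
- Level and power: "by using a significance level of 95% (p < .05), a power of 80"%. Sidedness is not stated; two-sided is assumed here.
- Effect: "a mean difference (MD) score of 1.0, and a standard deviation (SD within group) of 1.2", so d = 1.0/1.2 = 0.833 and f = d/2 = 0.417.
- Allocation 1:1, 2 groups, 2 measurements, and "a correlation among repeated measures of 0.95".
- 60% expected to complete treatment.

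**Step 1: reproduce the plan's figures.**
- The two-sample t-test needs 24 per arm (power 0.807); at 25 per arm power is 0.823.
- The repeated-measures between-groups formula has noncentrality f² x N x m / (1 + (m - 1) x rho), with m = 2 and rho = 0.95. At f = 0.417 and N = 48 this is 0.1736 x 48 x 2 / 1.95 = 8.55, giving power 0.816, or 24 per arm. With f rounded to 0.40, N = 50 is needed (power 0.801), which is 25 per arm.
- 25 / 0.60 = 41.7, rounded up to 42. Then 42 x 2 x 3 = 252.

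The sample-size arithmetic stands. The fault lies only in what is said to secure it.

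**Step 2: what blocking controls.** Stratified blocks of 2, 4 or 8 (sizes equally likely) were simulated for 252 consecutive entrants under several assumed mixes. The difference between arms within a subtype never exceeded 4. The subtype totals were set entirely by the mix.

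**Step 3: the most favorable mix.** Suppose each entrant is equally likely to be BN, BED or EDNOS (assumed) and recruitment stops at 252. The chance of exactly 84/84/84 is 252! / (84!)³ x (1/3)^252 = 0.003. The smallest of the six cells had a median of 38 (5th to 95th percentile 34 to 41). Such shortfalls are modest. The point is that nothing in the method ensures 42.

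**Step 4: uneven mixes.** The article gives no expected distribution, so these shares are assumptions. Power is for a two-sided two-sample t-test at d = 0.833 without baseline adjustment, noncentrality d x √(n/2).

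| Share of rarest subtype | Patients of 252 | Per arm | Completers per arm (60%) | Power, completers only | Power, outcome data from all |
|---|---|---|---|---|---|
| 20% | 50.4 | 25 | 15 | 0.596 | 0.823 |
| 15% | 37.8 | 19 | 11 | 0.460 | 0.705 |

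For n = 15 the noncentrality is 0.833 x √7.5 = 2.28; for n = 11 it is 0.833 x √5.5 = 1.95.

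**Step 5: the price of reaching 84 without a cap on the other subtypes.** The expected number of entrants is 84 / share: 84 / 0.25 = 336 and 84 / 0.20 = 420.

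**The case against.** **42 per cell may be a target.** The total is built upward from 42 per condition and subtype, and the six cells are named. The article nowhere says that recruitment stops at 252 whatever the mix. Enrolling each subtype until it reaches 84 fits the text, and a closing rule is the kind of detail that an article may leave to the full protocol. This stands to the extent that a shortfall cannot be called planned. It does not rescue the sentence, which names block randomization as the means.

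**The size of the loss is uncertain.** This stands, for four reasons.
- The 20% and 15% shares have no source in the article. The Background calls EDNOS, with BED included, the most common diagnosis, but the trial separates the two, and population prevalence is not enrolment share.
- The 60% is for completing treatment sessions. Under Study design, non-completers also receive questionnaires with the primary and secondary outcomes, and Statistical analysis plans intention-to-treat mixed models. The full-data column is an upper bound, since some data will be lost and non-completers may benefit less. Removing 40% from both arms is, however, the protocol's own convention.
- Waiting-list patients cannot leave a program that they have not started. With non-completion in the experimental arm only, 15 against 25 gives about 70% and 11 against 19 about 57%.
- A test on change from baseline could gain power. With a baseline correlation of 0.7 (assumed), 15 per arm gives 81% and 11 gives 67%; at 0.5 there is no gain; at the protocol's 0.95, power is near 100% even at 11.

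**Stronger readings.** A reader might infer that the whole trial is underpowered or its allocation flawed. The article does not support this: Study aims puts the primary question to the three diagnoses combined, the pooled comparison has about 126 per arm whatever the mix, and Statistical analysis makes the comparison between subtypes post hoc. A reader might also object that blocks of 2, 4 and 8 do not guarantee 42:42 even with exactly 84 in a stratum. That is true (exact balance in about 76% of simulated strata, maximum difference 4) but without consequence: power is 0.965 at both 42/42 and 40/44.

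**Conclusion.** The statement in Randomization is wrong as written. Stratified blocking keeps the arms approximately balanced within a subtype; it does not control subtype totals, and no rule in the article secures the 84 per subtype behind the total of 252. That conclusion needs no assumption about the mix.

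The practical harm is conditional. It arises only if recruitment stops at 252 in total and the mix is uneven. For a rarest subtype of 20% or 15%, the table in the working gives power from 46% to 82%, depending on the share and on how many patients give outcome data, before any gain from baseline adjustment. The consequence is confined to the subtype aim. The article does not show that a shortfall will occur, and a quota may exist in the full protocol.

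**What to change.** Reword the sentence to say that blocking keeps the two arms approximately balanced within each subtype. Keep 42 per cell as a recruitment target. Then state one of two rules:

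- **Close by stratum.** Each subtype closes to randomization once 84 patients have been randomized. This needs a counter in the web application. Its downside is slower recruitment of the rarest subtype. The article already describes access to the regular program outside the trial for patients who are not eligible.
- **Stop at 252 in total.** Say that subtype sizes are not controlled, and restate subtype power as a range over plausible mixes, saying whether it assumes completers only or outcome data from all randomized patients. This costs only the wording, but gives up the claim of 80% power in every subtype.

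If the full protocol already holds a quota, one sentence in the article is enough. A closing rule is useful only if it is set before the commonest subtype has passed 84.
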